### Data analysis

Statistical methods are used for analysing primary and secondary outcomes between the two groups and related factors. The main analysis is to compare the change from M0 to M1 in primary outcomes (patient activation and knowledge level) and secondary outcomes (QoL and risk of malnutrition) between IG and CG. Categorical variables will be described using frequencies and percentages. Continuous variables will be expressed as means with standard deviations for normally distributed variables and medians with interquartile ranges for non-normally distributed variables. The differences in changes between groups in continuous outcomes will be compared with two-sample t-test or Mann-Whitney U-test and the changes within groups with paired t-test or Wilcoxon signed rank test, as suitable. Logistic regression using generalised estimating equation (GEE) will be used to test the differences between and within groups at risk of malnutrition (classified as 0–2 and 3–7). Results will be presented using estimates of group differences with 95% confidence intervals. The effect of missing data on the results will be examined using sensitivity analysis. An intent-to-treat analysis will be applied and two-sided statistical tests with significance level of 0.05 will be used in the statistical analyses. Methods for any additional analyses are determined by the data.

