#### Clinical data

Clinical data is gathered from electronic patients’ records. We are interested to find out whether the educational intervention is related to better adherence to treatment schedule. Therefore, data of patient-induced treatment changes, cancellations, transferring and interruptions are documented from baseline to 8 weeks. It has been indicated that worse nutritional status is related to greater morbidity [17]. Therefore, we collect data of patients’ emergency room visits and hospitalisation from baseline to 8 weeks.

The sample size was calculated to detect a 7-point mean difference in the PAM scale between groups assuming standard deviation of 11 points for both groups with 80% power and significance level of 0.05. This leads to required sample size of 40 participants per group. The meaningful difference between the average score of individuals who engage in healthy behaviours and those who do not is considered 4 points on the PAM scale [44]. To reach the target sample size (40 + 40), the researcher recruits participants by sending questionnaires with a research info and contacting them by phone the day before they visit the outpatient clinic. The researcher also meets the eligible participants to provide verbal information of the trial and answer questions. The strategies to improve patients’ adherence to the intervention protocol comprise the use of a self-monitoring diary and positive feedback from the research nurse. For individual participants, the intervention will be discontinued in the case of worsening condition, treatment change, or at their own request.

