### Assignment of interventions

The researcher (LT) enrols the participants, and those willing to participate are randomly assigned to CG and IG using stratified randomisation according to stage of disease and existence of stoma. An allocation sequence using blockrand package [54] in R version 3.6.1 [55] was used. For each block, the block size was randomly chosen from a set of 2, 4 and 6. Allocation ratio of 1:1 was used. The statistician generated an unpredictable allocation sequence using sequentially numbered, opaque, sealed envelopes. The envelopes, numbered in advance, are opened sequentially after the participant’s name is written on the appropriate envelope [56]. The researcher (LT) allocates participants to the intervention with equal probability as a simple random sample is drawn from each group. Thus, the person enrolling participants does not know in advance which treatment the next person will get [39]. Patients' blinding is not possible as the RN informs the patients in IG of the one-hour educational session. The research nurse cannot be blinded because she provides the intervention. The data analyst is blinded as data are anonymised by using codes (001, 002 etc.).

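### The main test of the continuous outcomes compares unadjusted changes, without M0 or the stratification factors as covariates: valid, but it gives up precision the trial could have at almost no cost

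*Protocol article*

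**What the plan says.** The Data analysis section makes the change from M0 to M1, compared between arms, the main analysis for both primary outcomes (PAM, knowledge) and the secondary outcomes. For continuous outcomes it names the test: "The differences in changes between groups in continuous outcomes will be compared with two-sample t-test or Mann-Whitney U-test", whichever is suitable, with no criterion given. It also says that "two-sided statistical tests with significance level of 0.05 will be used in the statistical analyses" and promises group differences with 95% confidence intervals. Risk of malnutrition (NRS2002 in two classes) gets a GEE logistic model. No baseline covariate or stratification factor is named for any of these analyses.

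Under Assignment of interventions, patients are allocated by "stratified randomisation according to stage of disease and existence of stoma", and "Allocation ratio of 1:1 was used". Data collection lists PAM, the knowledge test, FACT-C and NRS2002 among the M0 questionnaires.

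The sample size, given at the end of Clinical data, was set to "detect a 7-point mean difference in the PAM scale between groups assuming standard deviation of 11 points for both groups". It does not say whether 11 is the SD of a PAM score at one visit or of the change, and it gives no M0–M1 correlation.

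**The concern.** A change score does use M0, but it subtracts it with a fixed slope of 1. When both visits have the same SD, the best slope is the correlation r, which is below 1 in practice, so subtracting the whole of M0 adds noise. A model that estimates the slope removes that noise.

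The strata raise a related issue. Stratified randomisation balances stage and stoma between arms, which makes the true variance of the treatment difference smaller if these factors are prognostic. A test that leaves them out does not see the reduction, so its standard error is too large.

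Finally, the trial was sized for a mean difference, and Mann-Whitney does not test one. If the choice of test waits for the distribution of the data, so does the choice of target.

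Precision is at stake, and in a trial of 80 patients there is little to spare.

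**Working it through.** **Inputs.** From the documents: difference 7, SD 11, 40 per arm, 1:1, two-sided 0.05. Assumed: r from 0.3 to 0.7, and equal SDs at M0 and M1.

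**The plan's own figure.** A two-sample t-test (non-central t) with 7/11 = 0.636 needs 39.7, so 40 per arm, and has 80.3% power at 40. The normal approximation gives 39. The stated 40 reproduces.

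**Formulas.**
- Variance of change = 2(1−r)·SD²
- Residual variance after adjusting M1 for M0 = (1−r²)·SD²
- Ratio, adjusted to change = (1−r²)/[2(1−r)] = (1+r)/2, below 1 for every r<1
- 95% CI half-width = t(0.975, 78)·SD·√(2/40), with t = 1.991

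**Reading A: 11 is the SD of a single score.** SD of change = 11√(2(1−r)); adjusted SD = 11√(1−r²).

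| r | SD change | SD adjusted | Power, change | Power, adjusted | Half-width, change | Half-width, adjusted |
|---|---|---|---|---|---|---|
| 0.3 | 13.0 | 10.5 | 66% | 84% | 5.8 | 4.7 |
| 0.5 | 11.0 | 9.5 | 80% | 90% | 4.9 | 4.2 |
| 0.7 | 8.5 | 7.9 | 95% | 98% | 3.8 | 3.5 |

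On this reading the planned test has less than the intended 80% power when r is below about 0.5.

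**Reading B: 11 is already the SD of the change.** The planned test has 80% power whatever r is. Adjusted SD = 11√((1+r)/2).

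| r | SD adjusted | Power, adjusted | Half-width, adjusted (change: 4.9) |
|---|---|---|---|
| 0.3 | 8.9 | 94% | 3.9 |
| 0.5 | 9.5 | 90% | 4.2 |
| 0.7 | 10.1 | 86% | 4.5 |

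**Stratification factors.** The documents do not say how strongly stage and stoma predict PAM, so I assume that they explain 0, 10 or 30% of the residual variance. I simulated 80 patients in 2×2 strata with permuted blocks of 2, 4 and 6, Reading A, r=0.5, 4000 replicates per scenario. The Monte Carlo standard error of a 5% rejection rate is √(0.05·0.95/4000) = 0.3 percentage points.

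| Variance explained by strata | Type I error, planned test | CI coverage, planned test | Half-width, planned test | Half-width with M0, stage, stoma |
|---|---|---|---|---|
| 0% | 0.052 | 94.8% | 4.9 | 4.3 |
| 10% | 0.038 | 96.2% | 4.9 | 4.0 |
| 30% | 0.030 | 97.0% | 4.9 | 3.6 |

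With M0 and both factors in the model, coverage was 95.4%, 95.6% and 94.7%. With M0 alone, type I error was still only 0.033 and 0.026 in the 10% and 30% rows, so the strata belong in the model as well as M0.

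**Choice of test.** The sample size rests on a mean difference. The t-test on changes targets that quantity; the rank test does not. The article gives no rule for choosing between them for either primary outcome.

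**The case against.** The strongest reply is that nothing here is invalid. In a randomised trial the t-test on changes is unbiased and does not inflate type I error; omitting the strata makes it conservative at worst, and only if they are prognostic. That stands: this is lost efficiency.

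The power shortfall also needs both Reading A and r below 0.5, and neither is documented. Since the main analysis is of change, Reading B is plausible, and power is then 80% as planned. That stands too, although adjustment gains under both readings. At r=0.7 on Reading A the gain is small.

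A covariate list can be left to an analysis plan, and the article does mention related factors. But the article names the tests for its main comparison, and neither can carry a covariate, so this is a choice already made. A criterion for choosing between the two tests could more reasonably sit in an analysis plan, and the analyst is blinded. That softens the point about Mann-Whitney without removing it.

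Three stronger readings are not supported:
- A reader might infer that the plan ignores M0. It does not; the change score subtracts it.
- A reader might infer that Mann-Whitney contradicts the promised confidence intervals. A Hodges-Lehmann shift estimate with its interval can accompany it.
- A reader might infer that the planned test would miss an observed difference of 4 points, which the protocol calls meaningful, and that adjustment would rescue it. In general it would not. On Reading A the smallest significant difference at r=0.5 is still 4.24 after adjustment for M0, and at r=0.7 it is already 3.79 without it. The trial was sized for 7 points; what happens at 4 depends mainly on the sample size.

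**Conclusion.** The point holds as a loss of precision and should be corrected. Adjusting for M0 leaves (1+r)/2 of the change-score variance: 65%, 75% and 85% at r = 0.3, 0.5 and 0.7. For the 7-point PAM effect this is worth about 18, 10 and 2 percentage points of power if 11 is a score SD, and about 13, 10 and 6 if it is the SD of change. The ratio is firm given equal SDs at the two visits. The power figures depend on r and on the meaning of SD 11, which the document does not give. The extra width from omitting stage and stoma depends wholly on how prognostic they are; it is nil if they are not. The open choice between t-test and Mann-Whitney is a smaller, separate weakness. The documents do not support a claim of bias, of inflated type I error or of a wrong sample size.

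**What to change.** For each of PAM, knowledge score and FACT-C, make the main between-group analysis a linear model of the M1 score on arm, M0 score, stage and stoma. Report the adjusted mean difference with its 95% CI. If residuals are clearly non-normal, keep the same estimate and use robust or bootstrap standard errors instead of switching to Mann-Whitney.

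Add stage and stoma to the GEE model for NRS2002. Do not add M0 there: the model is meant to test differences within as well as between groups, so M0 appears to be a response already.

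State whether SD 11 refers to the score or to the change.

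The cost is analysis wording and a few degrees of freedom. M0 is already collected, and stage and stoma are known at randomisation. In the logistic model the odds ratio becomes conditional on the strata, which the report should say. The article describes the trial as still recruiting, so at that point the change could be fixed before the data are analysed.

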## Methods

### Aim, design and setting of the study

The aim of this intervention is to improve patients’ empowerment in self-care. The design is a two-arm, single-centre trial with stratified randomisation (1:1) with repeated measures (Fig. 1). We hypothesise that patients with CRC who receive nurse-led empowering education of NIS vs standard education have higher self-care activation level, better knowledge level, less risk of malnutrition and less worsening of QoL at 2 months’ follow-up compared to the control group (CG).

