#### Risk of malnutrition

The risk of malnutrition is assessed as the educational intervention is presumed to prevent malnutrition or reduce the risk of malnutrition. In diagnostic assessment of malnutrition, the following criteria are recommended: non-volitional weight loss, low body mass index (BMI), reduced muscle mass, reduced food intake or assimilation and disease burden/inflammation [51]. To identify the patients at risk, we use the validated Nutritional Risk Screening 2002 tool (NRS2002) [52], which was developed to detect the presence of malnutrition and to predict whether malnutrition is likely to worsen due to patients’ illness [53]. Patients are assessed based on BMI, recent weight loss percentage and change in food intake (0–3 points), age (0–1 points) and severity of disease (0–3 points). The total sum is seven points. Patients with a total score of ≥3 are classified as nutritionally at risk.

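### The malnutrition-risk GEE, read as a test of change between arms, is valid but uses M0 inefficiently and does not directly report the hypothesised lower risk at 2 months

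*Protocol article*

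**What the plan says.** The hypothesis, under Aim, design and setting of the study, concerns follow-up: patients given the intervention should show "less risk of malnutrition and less worsening of QoL at 2 months’ follow-up compared to the control group".

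Data analysis then states that "The main analysis is to compare the change from M0 to M1 in primary outcomes", and the same sentence goes on to include the secondary outcomes, risk of malnutrition among them, compared between the intervention group (IG) and control group (CG). For the binary outcome, "Logistic regression using generalised estimating equation (GEE) will be used to test the differences between and within groups at risk of malnutrition". The cut-point is set under Risk of malnutrition: "Patients with a total score of ≥3 are classified as nutritionally at risk". Tests are two-sided at 0.05.

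The article does not say which terms enter the GEE, which coefficient is tested, or whether the arms share one M0 risk. It gives no at-risk proportion, correlation or power for this outcome.

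**The concern.** Comparing change in a binary outcome between two arms with a logistic GEE normally means fitting arm, visit and their product, and testing the product. The result is the M1 odds ratio divided by the M0 odds ratio.

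Baseline questionnaires are returned before the first clinic appointment, and patients are randomised after agreeing to take part. M0 therefore precedes allocation, and any M0 difference between arms is chance. The product term removes that chance difference in full, whether or not it predicts M1, and so adds its sampling error to the answer. Adjusting for M0, or giving both arms one M0 risk, removes only the part that M0 predicts.

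Two things are at stake. One is precision on a secondary outcome in a small trial. The other is the reported measure: a ratio of odds ratios does not tell a reader how much lower the risk is at 2 months.

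**Working it through.** **The plan's own figure.** The trial is sized on PAM alone: 7 points, SD 11, 80% power, two-sided 0.05. The normal approximation gives 2 × (1.960 + 0.842)² × 11² / 7² = 38.8, so 39 per group. The t-test gives 39.75, so 40, with 80.3% power. The stated 40 per group reproduces. No such figure exists for malnutrition risk.

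**Inputs.** From the protocol: 40 per arm, 1:1, two-sided 0.05, M0 before allocation. Assumed, because the protocol gives none: the M0 risk (equal in both arms), the M1 risks, and the M0–M1 correlation rho.

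**Formulas (log-odds scale, v = p(1 − p), n = 40).** Sum over the two arms:
- A = Σ 1/(n·v1)
- B = Σ 1/(n·v0)
- C = Σ rho/(n·√(v0·v1))

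The variance of the arm-by-time term with free M0 risks is A + B − 2C. The variance of the M1 contrast with one common M0 risk is A − C²/B. When the M0 and M1 variances are equal, the second divided by the first is (1 − rho²)/(2(1 − rho)) = (1 + rho)/2: 0.65, 0.70 and 0.75 at rho 0.3, 0.4 and 0.5.

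**Worked example: M0 35%, M1 50% (CG) versus 25% (IG), rho 0.3.**
- v0 = 0.2275; v1 = 0.25 and 0.1875. A = 0.2333, B = 0.2198, C = 0.0678. M1 log odds ratio (CG versus IG) = 1.0986.
- Arm-by-time: variance 0.3176, SE 0.564, z = 1.95, power 50%.
- Common M0 risk: variance 0.2124, SE 0.461, z = 2.38, power 66%.
- M1 alone, ignoring M0: variance 0.2333, SE 0.483, z = 2.27, power 62%.
- Chance imbalance: the SE of the M0 log odds ratio is √0.2198 = 0.469. A one-SE imbalance therefore multiplies or divides the arm-by-time estimate by e^0.469 = 1.60. The common-baseline contrast removes only C/B = 0.31 of it.

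**Closed form over a grid** (M0 20–40%, M1 gaps of 20 to 30 points). Gain of the common-M0 contrast over arm-by-time: 12 to 26 points at rho 0.3, 10 to 23 at 0.4, 7 to 20 at 0.5, 4 to 14 at 0.6 and 4 to 7 at 0.7. M1 alone is not a safe substitute: against arm-by-time it runs from +8 to +22 points at rho 0.3, from −4 to +7 at 0.5 and from −13 to −5 at 0.6.

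**Simulation** (20,000 trials, 40 per arm). Power of the arm-by-time logit test with sandwich variance, then of the M1 risk difference adjusted for M0 status with robust variance:

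| M0; M1 CG vs IG | rho 0.3 | rho 0.5 | rho 0.6 |
|---|---|---|---|
| 35%; 55% vs 30% | 49% / 67% | 63% / 75% | 73% / 82% |
| 50%; 65% vs 35% | 65% / 81% | 79% / 88% | 89% / 94% |
| 73%; 73% vs 45% | 55% / 77% | 70% / 85% | not attainable |

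The last cell is blank because those risks cannot have a correlation of 0.6. At rho 0.7 the middle row gains only about 1 point. For 10-point M1 gaps, simulation and closed form together give about 2 to 5 points, with power below 30% either way. Type I error is near 5% for both tests: 5.2–5.7% for the GEE and 5.0–5.3% for the adjusted comparison.

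**The case against.** A reader might infer that the GEE tests something other than the hypothesis, or that it is invalid. The protocol does not support that. With equal true M0 risks, the M0 odds ratio is 1, so the ratio of odds ratios equals the M1 odds ratio. Null and target are the same, and type I error is close to nominal. What remains is precision and the form of the reported estimate.

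A reader might also take the arm-by-time term and free M0 risks as stated. They are inferred. A GEE with a common M0 risk, or an M1 contrast from the same model, would fit the GEE sentence too, and an SAP could specify it. This stands. Still, the sentence naming change as the main comparison points away from those options, so the matter is more than omitted detail.

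A fixed loss of 9 to 22 points might be inferred as well. It rests on assumed M1 gaps of 25 to 30 points and rho of 0.3 to 0.5. NRS2002 includes age and disease severity, which may change little in 8 weeks, so a higher rho is plausible. The 73% base risk adds two categories from a cited geriatric gastrointestinal-cancer series and is not a design input.

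The choice of remedy matters too. A logistic regression of M1 on arm and M0 status meets sparse cells and separation at this size. At rho 0.6 its power relative to the arm-by-time GEE ran from +4 to −5 points, and adding stage and stoma would thin the cells further. The robust risk difference did not show this problem.

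Finally, percentages at risk would be described anyway, since the plan gives frequencies for categorical variables, and the outcome is secondary and unpowered. Both are true. They limit the weight of the point but do not remove it.

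**Conclusion.** The concern holds as one of efficiency and reporting, not of validity. On its natural reading, the planned between-arm comparison of change spends power on a baseline difference known to be chance, and it yields an estimate one step removed from the stated hypothesis.

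The size is conditional on the M0 risks being left free: about 9 to 22 percentage points for M1 gaps of 25 to 30 points at rho 0.3 to 0.5, about 1 to 9 points at rho 0.6 to 0.7, and about 2 to 5 points for a 10-point gap. All risks and correlations are assumptions. The direction was the same in every scenario tried with the common-M0 contrast or the robust adjusted risk difference. The primary outcomes and the sample size are not touched by this point.

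**What to change.** In Data analysis, state that for risk of malnutrition the tested contrast is the between-arm difference at M1, obtained in one of two ways:

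- from the GEE, with both arms constrained to one common M0 risk; or
- as an M1 risk difference adjusted for M0 status, with robust variance.

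Report the risk difference with its 95% CI. Add stage and stoma as covariates only if cell counts allow. M0 should not simply be dropped, because an M1-only comparison loses to the arm-by-time test at higher correlation.

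The cost is one or two sentences, with no new data and no more patients. The small downside is that the reported estimate is no longer the GEE ratio of odds ratios.

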#### Intervention protocol

The intervention was developed during autumn 2018 and spring 2019 by an interdisciplinary expert group consisting of two RN experienced in oncology, a clinical nutritionist, an oncologist, and the researcher (LT). We held four shared meetings and additional discussions between each member and the researcher. According to the protocol, patients in IG will receive knowledge of healthy diet and malnutrition. In addition, they will receive tailored knowledge of NIS. The tailoring is based on the side effect self-monitoring diary and patient activation level assessment according to the Patient Activation Measure (PAM) [35]. In addition, patients receive knowledge of the prevention of NIS and self-care strategies based on organisation guidelines. The teach-back method is used to verify participants’ understanding of the received knowledge, to tailor education, to uncover health beliefs, and to activate patients in dialogue [36]. Participants have to be able to teach back the main parts of the knowledge related to malnutrition as well as the reasons, prevalence, and self-care of the NIS they are suffering from. The teach-back method has shown a positive effect in self-care by improving outcomes in disease-specific knowledge, adherence and self-efficacy among people with chronic disease. It has also reduced hospital readmission rates [37].

Empowerment is supported by offering additional knowledge according to patients’ expectations. In addition, the research nurse uses active listening and strengthening self-care strategies that have been successful. The progression of the discourse is based on patients’ expectations and active involvement: the nurse provides the patient with expert knowledge and maintains an empathic connection to the patient throughout the session [38].

The content of the educational intervention is as follows:
Illustrating the purpose of the session.Exploring patients’ current knowledge of healthy diet and malnutrition, offering additional knowledge using teach-back.Bringing forward individual NIS and their intensity on a numerical rating scale (NRS) ≥3, and patients’ knowledge expectations, offering additional knowledge using teach-back.Bringing forward performed self-care strategies and offering additional knowledge using teach-back.Bringing forward individual NIS and their intensity (NRS < 3), offering additional knowledge.Making a brief summary.

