### Outcome measures

Primary outcomes are activation in self-care and knowledge level. Secondary outcomes are risk of malnutrition and QoL. The schedule of enrolment, interventions, and assessments [39] is presented in Fig. 2.

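### Two primary outcomes are each tested at two-sided 0.05 with no rule for combining them, and the sample size and power cover only one of them

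*Protocol article*

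**What the plan says.** Under Outcome measures: "Primary outcomes are activation in self-care and knowledge level". The Background and the Discussion also name the two together as primary, with neither ranked above the other.

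Under Data analysis: "The main analysis is to compare the change from M0 to M1 in primary outcomes (patient activation and knowledge level"), with the two secondary outcomes listed in the same sentence. The test is given once for all continuous outcomes: "The differences in changes between groups in continuous outcomes will be compared with two-sample t-test or Mann-Whitney U-test". The error level is also given once for everything: "two-sided statistical tests with significance level of 0.05 will be used in the statistical analyses".

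The sample-size paragraph, which sits under Clinical data, reads: "The sample size was calculated to detect a 7-point mean difference in the PAM scale between groups". Its other inputs are an SD of 11 in each arm, power of 80% and a level of 0.05, and it arrives at 40 patients per arm. No target difference, SD or power is given for the knowledge test, which is described under Knowledge level as 15 yes/no items scored by the number correct.

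On the link between the session and the test, Intervention protocol says: "Participants have to be able to teach back the main parts of the knowledge related to malnutrition". The same sentence extends this to the causes, frequency and self-care of the patient's own side effects.

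**The concern.** With two equal primaries there must be a rule that turns two p-values into one conclusion. The article fixes the level of each test and the power of one of them, but not that rule. The two obvious readings have different consequences:

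- **Either suffices.** Each test uses the full 0.05, so the pair does not hold 5%.
- **Both required.** Error is held, but the 80% power in the sample-size paragraph is not the power of the trial's primary conclusion.

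The stated 0.05 and the stated 80% therefore do not jointly describe the primary conclusion on either reading.

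A separate question is one of interpretation. The knowledge test covers malnutrition and the reasons for, manifestation and self-care of side effects. The session teaches this material and checks it by teach-back. A real gain in knowledge without a gain in activation is therefore plausible, and the text does not say whether that pattern would count as success. The Discussion makes implementation depend on the education proving effective, without defining effective in terms of the two primaries.

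**Working it through.** **1. Reproduce the stated sample size.** Inputs from the sample-size paragraph: difference 7, SD 11, power 80%, alpha 0.05. Two-sided testing comes from Data analysis.

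Normal approximation, per group: n = 2 × (1.960 + 0.842)² × 11² / 7² = 38.8, so 39. The two-sample t-test calculation gives 39.75, so 40. The stated 40 is reproduced. A one-sided test would need about 31-32 and does not match. The figure is therefore PAM alone at an unsplit two-sided 0.05. Power at 40 per group is 80.3% (t-test).

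**2. Either outcome suffices, and neither truly changes.** If the two tests are independent, P(at least one p < 0.05) = 1 − 0.95² = 0.0975. If the test statistics are bivariate normal with correlation ρ, it is 1 − P(|Z₁| < 1.96 and |Z₂| < 1.96):

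| ρ (assumed) | P(at least one false positive) |
|---|---|
| 0 | 9.8% |
| 0.3 | 9.5% |
| 0.5 | 9.1% |
| 0.7 | 8.3% |
| 0.8 | 7.8% |
| 0.9 | 7.0% |

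The upper bound under any dependence is 0.05 + 0.05 = 10%. The article gives no correlation. It describes PAM as measuring knowledge as well as skills and confidence, so a positive value is plausible. Up to ρ = 0.7 the range is about 8-10%.

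**3. Both required.** The chance of claiming success when at least one null is true is at most 5%. Joint power cannot exceed the smaller of the two powers, so it is at most PAM's 80.3%. Knowledge power is unknown. Two illustrations, assuming independence:

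- Knowledge power 80%: 0.803 × 0.80 = 64%.
- Knowledge power 95%: 0.803 × 0.95 = 76%.

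Positive correlation would raise both figures. They are not estimates for this trial.

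**4. What the remedies cost PAM.**

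- PAM tested first at 0.05: power stays at 80.3% with 40 per group.
- PAM tested at 0.025 (a Bonferroni split, or Holm when knowledge is not significant at 0.025): power at 40 per group is 71.2%. Restoring 80% would take 49 per group by the t-test, 98 in total against 80.

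**5. Why a fixed sequence holds 5%.** If the PAM null is true, any false claim requires PAM to be significant, which has probability at most 0.05. If it is false, the only possible false claim is on knowledge, again at most 0.05. Correlation does not enter.

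**The case against.** The strongest reply is that nothing in the article says a positive result on either outcome is enough. A general 0.05 level is compatible with a fixed sequence, with Holm, or with requiring both, and a SAP that is not shown may contain the rule. The sizing on PAM, the stated aim of empowerment in self-care, and the abstract's closing question about self-care activity all lean towards PAM as the lead outcome.

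Much of this stands. The 8-10% is conditional, and the absence of a rule alone could be left to a SAP. What remains is that the article itself ranks the two outcomes equally, sets 0.05 for every test and attaches its only power statement to PAM. A SAP that split alpha would contradict the sample-size paragraph, and one that required both would make the 80% inapplicable. A PAM-first order would fit the sizing, but the article does not state it.

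A reader might go further and infer that a likely knowledge gain would produce a positive trial at nearly double the stated error rate. The documents do not support that. If the knowledge gain is real, a significant knowledge result is not a false positive, and the one remaining primary null, PAM, is still tested at 5%. The 8-10% needs both nulls to be true, so the two arguments cannot be added together. Nor should 64% be read as the price of requiring both. It rests on an assumed 80% power for knowledge, and if a knowledge gain is likely that power could be much higher.

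**Conclusion.** The point holds in conditional form. As written, the primary conclusion has no defined error rate or power. The chance of a false positive primary claim is about 8-10% if either outcome suffices, if neither truly changes, and if the correlation between the tests is between 0 and about 0.7 (assumed). If both are required, error is held at 5%, and power is no more than PAM's 80% and otherwise unknown. Whether a knowledge gain alone would count as success is also open, but that is a matter of interpretation and not of error rate.

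The PAM comparison, its 5% level, its power and the 40 per group are unaffected. The defect is in how results will be combined and claimed. It should be fixed before the analysis, but it does not undermine the design.

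**What to change.** In Data analysis, state a fixed sequence: PAM change is tested first at two-sided 0.05, and the knowledge score is tested confirmatorily at two-sided 0.05 only if PAM is significant. Otherwise knowledge is reported with its estimate and confidence interval, without a confirmatory claim. In the sample-size paragraph, state that the 80% power refers to PAM. If a SAP exists, it should say the same.

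This leaves 40 + 40 patients, data collection and PAM's power unchanged, and it follows the article's own sizing and self-care aim. The cost is that knowledge, which the authors chose as a primary outcome, cannot carry a confirmatory claim on its own. As the trial is registered and recruiting, the change should be documented as an amendment made without sight of results by group.

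If the sponsor wants the two outcomes to keep equal standing, Holm is the alternative. It also holds 5% for the pair, but PAM power falls to about 71% whenever PAM has to be tested at 0.025.
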